## Abstract

**Background:**

Prostate cancer is the most commonly diagnosed non-melanoma cancer among men. Androgen deprivation therapy (ADT) has been the core therapy for men with advanced prostate cancer. It is only in recent years that clinicians began to recognize the cognitive-psychosocial side effects from ADT, which significantly compromise the quality of life of prostate cancer survivors. The objectives of the study are to determine the efficacy of a simple and accessible home-based, walking exercise program in promoting cognitive and psychosocial functions of men with prostate cancer receiving ADT.

**Methods:**

A 6-month prospective, single-blinded, randomized controlled trial will be conducted to compare the Exercise Group with the Control Group. Twenty men with prostate cancer starting ADT will be recruited and randomly assigned to one of the two groups: the Exercise Group will receive instructions in setting up an individualized 6-month home-based, walking exercise program, while the Control Group will receive standard medical advice from the attending physician. The primary outcomes will be psychosocial and cognitive functions. Cognitive functions including memory, attention, working memory, and executive function will be assessed using a battery of neurocognitive tests at baseline and 6 months. Psychosocial functions including depression, anxiety and self-esteem will be assessed at baseline, 3 and 6 months using the Center for Epidemiological Studies Depression Scale, Spielberger State-Trait Anxiety Inventory, and Rosenberg Self-Esteem Scale*.*

**Discussion:**

The significance of the cognitive-psychosocial side effects of ADT in men with prostate cancer has only been recently recognized, and the management remains unclear. This study addresses this issue by designing a simple and accessible home-based, exercise program that may potentially have significant impact on reducing the cognitive and psychosocial side effects of ADT, and ultimately improving the health-related quality of life in men with prostate cancer receiving ADT.

**Trial registration:**

NCT00856102

## Background

In North America, prostate cancer is the most commonly diagnosed non-melanoma skin cancer. It is estimated that 25,500 men in Canada [1] and over 2.3 million men in the United States have prostate cancer [2]. More than one-third of men with prostate cancer will develop recurrent disease and receive androgen deprivation therapy (ADT) [3]. ADT is accomplished by bilateral orchiectomy or the use of a luteinizing hormone-releasing hormone agonist. The duration of response to ADT using hormone agonist ranges from 12 to 18 months, with 20% of patients having a complete prostate specific antigen response at 5 years [4]. However, there are a number of long-term health, cognitive, and psychosocial sequelae from ADT that significantly impact the health-related quality of life of men with prostate cancer.

The cognitive-psychosocial side effects of ADT are distinct health care needs of prostate cancer survivors that are not recognized until recent years. Studies have revealed that men receiving ADT have reduced cognitive function and self-esteem, and increased depression and anxiety secondary to the therapeutically-induced reduction of testosterone level [5-12]. Cognitive domains that are most significantly affected include verbal memory and learning [6,7], spatial memory and ability [5,8], visuomotor skills [10], executive function [6], and attention [7]. Men with prostate cancer receiving ADT are at a particularly higher risk of developing cognitive and depressive disorders than men without cancer [11]. These cognitive-psychosocial problems associated with ADT result in a significant reduction of health-related quality of life of prostate cancer survivors.

Physical activities through exercise is a lifestyle intervention that has protective effect against the risk of developing depression and anxiety disorders in the general population [13-15], and also improve cognitive function in older adults [16-18]. Regular exercise improves cardiovascular fitness, which in turn associates positively with cognitive performance in older adults and may have protective effect against cognitive decline later in life [19-23]. The underlying mechanism of how exercise improves cognitive and psychosocial functions are not clear. However, evidence suggests that increases in hippocampal volume [24,25] and brain monoaminergic systems [26] are possible mediating factors for improved memory function in individuals with higher cardiovascular fitness levels. Exercise, therefore, could have a potentially significant impact on improving the mental health and health-related quality of life of prostate cancer survivors.

Walking, in particular, is a simple and easily accessible form of exercise that can be readily incorporated into the long-term lifestyle of cancer survivors. Walking exercise has vast benefits on the quality of life and overall health including cognitive function in older adults [27,28]. In women with breast cancer, walking exercise has shown to significantly improve their health-related quality of life, fatigue, physical and mental health, [29-34] and even overall survival rate [35,36]. In men with prostate cancer on ADT, studies that investigated the role of exercise utilized mostly resistance exercise or a combination of resistance and aerobic trainings [37]. The results demonstrated that exercise could significantly reduce fatigue, improve muscular strength, physical function and overall health-related quality of life in men with prostate cancer. However, the effect of exercise, specifically walking, in the cognitive-psychosocial functions of men with prostate cancer on ADT is unknown. Therefore it is imperative to investigate if a simple walking exercise program will improve cognitive-psychosocial functions of men with prostate cancer on ADT.

The objective of the study is to determine the efficacy of a simple and accessible home-based walking exercise program in promoting cognitive-psychosocial functions of men with prostate cancer receiving ADT.

## Methods

A 6-month prospective, assessor-blinded, randomized controlled trial will be conducted to compare an Exercise Group to a Control Group. Patients will be recruited through CancerCare Manitoba. Baseline and follow-up visits will be conducted at the Department of Physical Therapy at the University of Manitoba. The University of Manitoba Research Ethics Board has approved the study protocol (Ethics Reference # H2008:318), which is also in compliance with the Helsinki Declaration.

### Participants

#### Inclusion criteria

Patients will be included in the study if they are men aged 50 years or older, diagnosed with adenocarcinoma prostate cancer, and will initiate and receive continuous ADT (luteinizing hormone releasing hormone agonist (LHRH) or combination of LHRH and anti-androgen) for at least 6 months after recruitment. Patients will be required to provide written informed consent to participate in the study.

#### Exclusion criteria

Patients will be excluded from the study if they have severe cardiac disease (New York Heart Association class III or greater), angina, pre-existing osteoporosis with T-score at or below −2.5, stable bone lesion, uncontrolled hypertension (blood pressure > 160/95 mm Hg), moderate to severe aortic stenosis, acute illness or fever, uncontrolled atrial or ventricular dysrhythmias, uncontrolled sinus tachycardia (> 120 beats per minute), third-degree atrio-ventricular heart block, active pericarditis or myocarditis, recent pulmonary embolism, deep vein thrombosis, uncontrolled diabetes, uncontrolled pain, cognitive impairment, history of falls due to balance impairment or lost of consciousness, or severe neuromusculoskeletal conditions that limit their ability to perform walking exercise (including ataxia, peripheral or sensory neuropathy, unstable bone lesion, severe arthritis, pathological lower limb fractures within 6 months, lower limb amputation).

#### Recruitment

A total of 20 patients will be recruited consecutively during office visits at the initial 3-month phase of the study at CancerCare Manitoba. The attending physician will screen the patients for inclusion criteria (men aged 50 or older, diagnosed with adenocarcinoma prostate cancer, will initiate and receive continuous ADT (LHRH or combination of LHRH and anti-androgen for at least 6 months). The physicians will be provided with an information sheet that provides brief information about study. If the patients meet the preliminary inclusion criteria, the physicians will provide a brief explanation about the study, and verbal consent to refer them to a clinical research nurse. The clinical research nurse will confirm that all inclusion and exclusion criteria are met, explain the study protocol, provide an information sheet for patients, and obtain written informed consent from the patients who would like to participate in the study. The clinical research nurse will provide the student research assistant (SRA) with the signed consent forms and contact information of the consented patients of the study.

### Assessment sessions

Each participant will attend a total of three assessment sessions: one baseline, and two follow-up sessions at 3 and 6 months after ADT initiation at the Department of Physical Therapy. The Exercise Group will complete telephone survey between follow-up sessions.

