#### Baseline assessment session

The SRA, who is trained in health sciences field, will contact the participants to schedule a baseline assessment in coordination with a clinical psychology research assistant (CPRA), who is trained to administer neuropsychological tests.

The baseline assessment will be administered by the CPRA first, followed by the SRA. The CPRA will collect the sociodemographic characteristics, and administer the primary (cognitive-psychosocial functions) and secondary outcome measures (health related quality of life (HRQOL)). The SRA will collect data on the physical activity variables.

The CPRA will be blinded to the group assignments of the participants. After the baseline assessment, the SRA will assign the participant the first available number from a randomly generated list consisting of “1” and “2”, that are generated by mixed randomization, [38] using both simple randomization and permuted-block methods. Number “1” is designated as the Exercise Group that will receive instructions in setting up an individualized 6-month home-based walking exercise program in addition to their daily activities. Number “2” is designated as the Control Group that will be advised to perform daily activities as usual and follow the standard medical advice from their attending physician.

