#### Follow-up sessions

The CPRA will schedule follow-up sessions for all participants at 3 and 6 months after ADT initiation. At 3 months, primary outcome (psychosocial functions) and secondary outcome variables (HRQOL) will be re-assessed. At 6 months, all primary (cognitive and psychosocial functions) and secondary (HRQOL) outcome measures will be re-assessed.

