### Data collection

At baseline session, the CRN will collect clinical data from the medical records of all consented patients that will include current cancer stage, time since diagnosis, treatment intent, testosterone level, prostate specific antigen level, Gleason score, comorbidity index. The SRA will collect sociodemographic data including age, marital status, ethnicity, living arrangement, education, work status, alcohol consumption and smoking history.

At baseline and 6-month follow-up visits, the primary outcome variable of *cognitive function* including memory, attention and working memory, and executive function will be assessed by the CPRA using well-established neurocognitive tests. Additionally, each participant will complete a standardized “effort test” to ensure validity of the test results. A minimum of 6 months between tests is required to prevent practice or carry-over effects. *Memory* will be assessed using: (1) the Brief Visuospatial Memory Test - Revised (BVMT-R) [44] for non-verbal memory, and (2) the California Verbal Learning Test, 2^nd^ Edition (CVLT-II) [45] for verbal memory. *Attention and working memory* will be assessed using: (3) the Digit Span and Letter-Number Sequencing tasks from the Wechsler Adult Intelligence Scale – 3^rd^ Edition (WAIS-III). [46]*Executive function* will be assessed using: (4) the Stroop Color and Word Test [47] for processing speed and inhibition, and (5) the Trail Making Test Parts A and B [48] for visuomotor tracking and mental flexibility. *Test-taking effort* of the neurocognitive tests will be confirmed using the (6) Word Memory Test (WMT) [49].

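### Follow-up visits are counted from ADT start but exercise and the retest interval run from baseline; unless baseline testing is on or before ADT start, the final test breaks the 6-month retest minimum

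*Protocol article*

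**What the plan says.** Four statements in the protocol article set the timing.

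- **Visits.** Assessment sessions plans "one baseline, and two follow-up sessions at 3 and 6 months after ADT initiation". Follow-up sessions repeats this for everyone: "The CPRA will schedule follow-up sessions for all participants at 3 and 6 months after ADT initiation".
- **Allocation and intervention.** Baseline assessment session says "After the baseline assessment, the SRA will assign the participant the first available number", and the Exercise Group then receives instruction in an "individualized 6-month home-based walking exercise program".
- **Retest interval.** Data collection states: "A minimum of 6 months between tests is required to prevent practice or carry-over effects". The neurocognitive battery is given only at baseline and at the 6-month visit.
- **Eligibility.** Inclusion criteria admits men who "will initiate and receive continuous ADT", so recruitment is described as coming before ADT. Recruitment uses the same future tense.

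The baseline visit comes later than recruitment. The Methods and Recruitment sections describe screening by the physician, referral to a research nurse, written consent and handover to the student assistant. The student assistant then books the baseline appointment jointly with the psychology assistant, at a different site from the clinic. No statement places that visit on or before the day ADT begins.

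**The concern.** The article uses two time origins as if they were one. The follow-up visits run from ADT start. The exercise programme and the retest interval run from the baseline visit. Nothing ties the two dates together, so the gap between them goes straight into the retest interval and into the amount of exercise done by the primary time point.

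The cognitive primary outcome rests on a single pair of measurements, and the article itself says that too short an interval invites practice or carry-over effects. A late baseline would therefore break a validity rule that the trial set for itself. It would also test men who have spent less time at the full exercise level, and their baseline would no longer be a pre-ADT measurement. The 3-month psychosocial visit shifts by the same amount. With 20 men in total, variation of purely administrative origin is hard to absorb.

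**Working it through.** **Inputs**

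- Final visit: 6 months after ADT start (Assessment sessions; Follow-up sessions), taken as 26 weeks. The 3-month visit is taken as 13 weeks.
- Minimum interval between cognitive tests: 6 months (Data collection), also 26 weeks.
- Full exercise level: reached at about 18 to 20 weeks and then held (Exercise group protocol). This is taken as given.
- Exercise start: the article gives no date. A start at the baseline visit is inferred from Baseline assessment session and Exercise group protocol; a later start would shorten exposure further.
- L = date of baseline visit minus date of ADT start, in weeks. **The article does not give L, so the values below are assumptions.** Negative L means that baseline comes before ADT.

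**Formulas**

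- Retest interval = maximum exercise exposure at the final test = 26 − L.
- Weeks at full level before the final test = (26 − L) − 20 to (26 − L) − 18.
- Weeks from baseline to the 3-month visit = 13 − L.

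**The plan's own figure.** At L = 0 the retest interval is 26 − 0 = 26 weeks, which is exactly the 6-month minimum. There is no slack for a visit held a few days early.

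**Results**

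| L (weeks, assumed) | Retest interval and maximum exercise exposure (weeks) | 6-month minimum met? | Weeks at full level | Baseline to 3-month visit (weeks) |
|---|---|---|---|---|
| −4 | 30 | yes | 10–12 | 17 |
| −2 | 28 | yes | 8–10 | 15 |
| 0 | 26 | yes, just | 6–8 | 13 |
| +1 | 25 | no | 5–7 | 12 |
| +2 | 24 | no | 4–6 | 11 |
| +4 | 22 | no | 2–4 | 9 |

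The minimum is met if and only if 26 − L ≥ 26, that is, L ≤ 0. For any positive L the visit rule and the retest rule cannot both be followed. For negative L the minimum holds, but the retest interval and exercise exposure differ between men by the lead time.

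**After the fix.** If visits are counted from baseline, the retest interval is 26 weeks for every L, provided that the visit window does not open early. ADT exposure at the final visit then becomes 26 + L weeks: 22 at L = −4 and 30 at L = +4.

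**The case against.** The strongest reply is that the rules are compatible as intended. The eligibility criteria look forward to ADT, a baseline in such men is most naturally a pre-ADT baseline, and the 6-month retest rule can itself be read as a constraint that scheduling must respect. Read together, these imply baseline no later than ADT start. This largely stands as an account of intent. It does not settle the matter, because the future tense governs recruitment and the baseline visit is arranged afterwards through several steps.

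Counting visits from ADT start is also defensible in a trial about the effects of ADT, because it equalises ADT exposure at each visit. That is a real advantage, and changing the origin gives some of it up. An article may also leave visit windows to the full protocol. That is fair, and the missing window is not the point here: the point is two stated origins and a mandatory minimum that can conflict.

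A reader might go further in three ways that the article does not support.

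- *That men are identified at the very visit where ADT is begun, so a late baseline is to be expected.* Recruitment says only that men are recruited during office visits and have yet to start ADT.
- *That with an early baseline the programme stops before the final test.* The programme is labelled as 6 months long, but Exercise group protocol has the attained level kept up until the study ends, so exercise can be read as continuing to the last visit.
- *That the timing biases the comparison between arms.* Allocation follows baseline, both arms share the same visit origin, and the planned test is a group-by-time interaction.

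**Conclusion.** The point holds in conditional form. The visit rule, the start of the programme and the retest minimum agree on the 6-month minimum only when baseline testing falls on or before ADT start, and the article does not require that. With an assumed lag of 1 to 4 weeks, the retest interval and maximum exercise exposure are 25 to 22 weeks instead of at least 26. Time at the full exercise level falls from 6–8 weeks to 5–7 weeks at a 1-week lag and 2–4 weeks at a 4-week lag. With baseline before ADT the minimum is safe, but interval and exposure still vary between men.

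The consequence is added variability and a possible practice effect in both arms. The size depends wholly on the unstated lag and on exercise starting at the baseline visit; the added noise itself cannot be quantified from the article. It would be too strong to call this a contradiction in every case, or a flaw that invalidates the comparison. It is a scheduling inconsistency that is worth correcting and cheap to correct.

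**What to change.** Reconcile Assessment sessions, Follow-up sessions and Data collection by using one time origin:

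1. Count the 3- and 6-month visits from the baseline assessment/randomisation, not from ADT start.
2. State that the final cognitive test takes place no earlier than 6 months after the baseline test.
3. Schedule baseline testing on or before ADT start where this is feasible without delaying ADT.
4. Record the interval from ADT start to baseline for each man and report it by arm.

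**Cost.** Wording in the visit sections and one recorded date. ADT exposure at each visit will vary with the lag. Where baseline follows ADT start, final visits move later by the same number of weeks.

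A smaller alternative keeps the ADT origin and requires baseline on or before ADT start. That secures the retest minimum if the final visit is not held early, but retest interval and exercise exposure would still vary with the lead time.

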#### Baseline assessment session

The SRA, who is trained in health sciences field, will contact the participants to schedule a baseline assessment in coordination with a clinical psychology research assistant (CPRA), who is trained to administer neuropsychological tests.

The baseline assessment will be administered by the CPRA first, followed by the SRA. The CPRA will collect the sociodemographic characteristics, and administer the primary (cognitive-psychosocial functions) and secondary outcome measures (health related quality of life (HRQOL)). The SRA will collect data on the physical activity variables.

The CPRA will be blinded to the group assignments of the participants. After the baseline assessment, the SRA will assign the participant the first available number from a randomly generated list consisting of “1” and “2”, that are generated by mixed randomization, [38] using both simple randomization and permuted-block methods. Number “1” is designated as the Exercise Group that will receive instructions in setting up an individualized 6-month home-based walking exercise program in addition to their daily activities. Number “2” is designated as the Control Group that will be advised to perform daily activities as usual and follow the standard medical advice from their attending physician.

#### Follow-up sessions

The CPRA will schedule follow-up sessions for all participants at 3 and 6 months after ADT initiation. At 3 months, primary outcome (psychosocial functions) and secondary outcome variables (HRQOL) will be re-assessed. At 6 months, all primary (cognitive and psychosocial functions) and secondary (HRQOL) outcome measures will be re-assessed.

### Control group protocol

The SRA will provide each participant of the Control Group with a pedometer to monitor his ambulatory activities. The participants will also be provided with a take-home package that includes written instructions, pedometer daily logs, and self-addressed envelopes. The participants will be instructed to wear the pedometer during waking hours, except while bathing, swimming or any procedures that do not allow metal parts to be close to targeted treatment area. The pedometer will be worn on a waistband, at or slightly anterior to the mid-axillary placement. A 50-step preferred-pace trial walk will be used to determine the side of pedometer placement. The side that yields the least percentage error in step counts will be the side for the individual’s daily application [39]. At the end of each day, participants will record the date, total daily time wearing the pedometer, and the number of daily steps taken, and then reset the pedometer to zero. Every two weeks, the SRA will call the participants to check for concerns and remind them to return their pedometer daily logs using the self-addressed envelopes.

